### Reimbursements

Participants in both conditions will receive an Aus $15 (US $11.59) e-gift voucher to thank them for their time and completion of the posttest survey. They will also receive an Aus $15 (US $11.59) e-gift voucher after completing the follow-up survey. All e-gift cards will be emailed within 5 working days of a participant completing the survey and will be issued through GiftPay.

### Outcome Measures

Table 1 shows the administration schedule of measures.

**Table 1 table1:** Schedule of outcome measures.

Measure	Data collection timepoint		
	Baseline	Posttest (10 weeks)	Follow-up (22 weeks)
Demographics and background	✓^a^	—^b^	—
Experience of mental health	✓	—	—
Self-care	✓	✓	✓
Experience in mental health training	✓	—	—
School factors	✓	✓	✓
Impact of COVID-19 on helping behaviors	✓	✓	✓
Perceived mental health knowledge and awareness	✓	✓	✓
Mental health knowledge	✓	✓	✓
Stigma	✓	✓	✓
Confidence	✓	✓	✓
Helping behaviors	✓	✓	✓
Psychological distress	✓	✓	✓
Module recommendation question	✓	—	—
Barriers to use	—	✓	—
Program satisfaction	—	✓	—
Process evaluation	—	✓	—
Program impact on future behaviors	—	—	✓

^a^Indicates the timepoint measure is administered.

^b^Indicates the measure is not administered at that timepoint.

#### Primary Outcome Measure

The primary outcome for this trial is educators’ confidence in recognizing and responding to students’ mental health needs. This is measured using an adapted version of the confidence to recognize, refer, and support subscale from the study by Sebbens et al [31]. Participants are asked to rate how confident they feel about a set of 15 scenarios (eg, *recognizing a student with mental health problems*) using a 5-point Likert scale ranging from 1 (*not at all confident*) to 5 (*very confident*). Mean total scores are calculated to represent participants’ self-reported confidence in managing their students’ mental health needs. Total scores can range from 15 to 75, with higher scores indicating greater levels of confidence. Scores will be compared over time and between the intervention and control arms at each time point.

#### Secondary Outcome Measures

##### Helping Behaviors for Mental Health

A modified version of the Help Provided to Students Questionnaire by Jorm et al [16] is used to assess the frequency of helping behaviors for mental health among educators. Participants indicate how often they have engaged in 13 helping behaviors (eg, *spent time calming a student down*) during the past 2 months. This is answered using a 4-point scale (*never*, *once*, *occasionally*, *frequently*). Items are then summed to create a total score (range: 15 to 60), with higher scores indicating a greater frequency of helping behaviors.

##### Perceived Mental Health Knowledge and Awareness

This is assessed using the Perceived Knowledge and the Perceived Awareness subscales from the Mental Health Literacy and Capacity Survey for Educators [32]. Participants are asked to rate their level of perceived knowledge on a set of 4 statements (eg, *how would you rate your knowledge of the signs and symptoms of student mental health issues*) from 0 (*not at all*) to 4 (*extremely*). Items are then summed to create a total score (range: 0-16), with higher scores indicating greater knowledge of mental health.

For the awareness subscale, participants are asked to rate their level of perceived awareness on a set of 5 statements (eg, *how would you rate your awareness of the risk factors and causes of student mental health issues*) from 0 (*not at all*) to 4 (*extremely*). Items are then summed to create a total score (range: 0-20), with higher scores indicating greater awareness of mental health issues.

##### Mental Health Knowledge

This consists of 2 constructs: mental health literacy and the recognition of common mental illnesses. These 2 constructs are measured using an adapted version of the 12-item Mental Health Knowledge Schedule (MAKS; [33]) and 2 vignettes adapted from the study by Jorm and Wright [34]. To measure mental health literacy, participants are asked to rate how much they agree with the first 6 items on the MAKS (eg, *Most students with mental health problems want to complete their schooling*) using a Likert scale ranging from 1 (*strongly disagree*) to 5 (*strongly agree*). Items are then summed to create a total score (range: 6-30), with higher scores indicating higher mental health literacy. Recognition of common mental illnesses is assessed using the remaining 6 items from the adapted MAKS (items 7-12), where participants are asked to rate whether they believe the conditions of depression, stress, grief, anxiety, self-harm, and substance misuse are mental illnesses using a Likert scale ranging from 1 (*strongly disagree*) to 5 (*strongly agree*). Participants are also asked to read 2 vignettes adapted from the study by Jorm and Wright [34]. These vignettes describe 2 adolescents with depression or anxiety, and the participants are asked to indicate which mental illness they believe the scenario depicts (free response).

##### Stigma

A modified version of the Personal Stigma subscale from the Depression Stigma Scale from Griffiths et al [35] is used to measure stigma toward mental health illnesses. Participants are asked to rate how much they agree with 9 statements (eg, *students with a mental illness could snap out of it if they wanted*) using a Likert scale ranging from 1 (*strongly disagree*) to 5 (*strongly agree*). Items are then summed to create a total score (range: 9-45), with higher scores indicating greater levels of stigma.

##### Psychological Distress

The Distress Questionnaire-5 (DQ-5) [36] is used to assess the personal psychological distress of educators. Participants are asked to rate how frequently, in the past 6 weeks, they have experienced 5 symptoms (eg, *Thinking back over the past 6 weeks, how often have you felt hopeless*). Answers are given using a 5-point scale ranging from 1 (*never*) to 5 (*always*). Items are then summed to create a total score (range: 5-25), with higher scores indicating greater levels of psychological distress. The DQ-5 has high internal consistency and convergent validity [36,37].

#### Supplementary Measures

##### Demographics and Background Factors

Participants are asked to provide their name, age, gender identity, whether they identify as Aboriginal or Torres Strait Islander, current role at their school, duration of employment at their current school (years), overall experience as an educator (years), and experience in their current role (years) at baseline.

##### Experience of Mental Illness

Participants are asked to indicate whether they have had a personal, family, or close friend experience a mental illness (answered *yes* or *no* or *prefer not to answer*).

Participants are also asked to rate how frequently they engage in self-care. This is to be answered on a 6-point scale (*never*, *less than once a month*, *once a month*, *a few times a month*, *weekly*, or *daily*).

##### Experience in Mental Health Training

Participants are asked to rate how important they believe mental health training is for educators (answered 0, *not at all important* to 4, *extremely important*), how they rate their level of mental health training (answered 0 *none to date* to 3 *extensive training*), the mental health training programs they have completed (free response), and how confident they are that an online program can meet their training needs (answered 0 *not at all confident* to 4 *extremely confident*).

##### School Factors

Participants are asked to indicate their school location (*metropolitan*, *regional*, or *rural*), school type (*government*, *Catholic*, or *independent*), and whether their school is same sex (answered *yes* or *no*). Participants are also asked to indicate whether their school has a student well-being policy (answered *yes* or *no*) and staffing roles to support students’ mental health (answered *yes* or *no*). Participants are also asked to rate the degree to which mental health is their school’s priority (answered 0 *not a priority* to 4 *high priority*) and how responsible they feel for their students’ mental health and well-being (answered 0 *not at all responsible* to 4 *completely responsible*). Participants are also asked to indicate, on average, the hours per week they spend supporting students’ mental health needs and how supported they feel by their colleagues, supervisor or employer, workplace, friends, and family (answered 0 *not at all* to 4 *extremely*).

##### Impact of COVID-19 on Helping Behaviors

In response to COVID-19, participants in this trial are asked questions regarding helping behaviors that may have changed due to the pandemic. The first 3 questions, “Have you reached out to students in a way that is different than you have done so in the past because of COVID-19? (eg, connecting via technology)?”, “Have you implemented a service, program, or educational information session about mental health?”, and “Are there any other ways you have responded to your students’ mental health that isn’t covered here?” will require a *yes* or *no* response. If a participant answered *yes* to the latter 2 questions, they were asked to specify (free response). Participants are also asked how often then have contacted their students about mental health using technology (email or school e-learning platform); this is answered using a 4-point ordinal scale from 1 (*never*) to 4 (*frequently*).

#### Measures for Intervention Participants Only

The following measures will be obtained only from participants assigned to BEAM and will be used in subsequent research into factors that may moderate or mediate outcomes.

##### Program Use

Program use will be measured by the number of completed lessons (maximum of 27), collected automatically by the eHealth research platform.

##### Barriers to Use

Program barriers will be identified using a 13-item list at posttest.

Participants will be asked to report if they experienced any of the listed barriers throughout the trial (eg, *Forgot about it* and *Didn’t have enough time*); this is answered as *yes* or *no*. If a participant answers *yes* to the 13th item *Other not listed above (Please specify)*, a mandatory free response textbox will appear for the participant to provide more detail.

##### Program Satisfaction

Participants are asked to rate the extent to which they agreed with a set of 14 statements about the BEAM program (such as *I enjoyed using BEAM* and *the content was easy to understand*). This is answered using a 5-point Likert scale ranging from 1 (*strongly disagree*) to 5 (*strongly agree*).

##### Process Evaluation

Participants are asked whether they completed the peer coaching activities with a colleague (answered *yes* or *no*), and if yes, how frequently they met (*more than once a week*, *about once a week*, *about once a fortnight*, and *about once a month*) and whether they found these activities to be valuable (answered *yes*, *no*, or *not appropriate*). Participants are also asked “What could we do to improve the program,” “Is there any content or topics you would have liked to have been covered in the training?”, and “Is there anything else you would like to say about the program and its value for you?” (all answered with free responses). Finally, participants are asked what device they completed the program on (eg, laptop, tablet, or mobile).

##### Program Impact on Future Behaviors

Participants are asked to indicate whether the program content or resources were shared with other school staff and if any well-being programs had been implemented during the trial period (answered *yes* or *no*). If they answer *yes,* participants are asked to provide more detail (free response).

#### Statistical Methods

The primary analysis will use a mixed model repeated measures analysis of variance (MMRM), accounting for repeated assessments within individuals and a random effect to account for clustering within schools. Models will include the factors time, condition (intervention vs control), and their interaction, with the critical test of effectiveness being planned contrasts of this interaction from baseline to postintervention (the trial primary endpoint) and follow-up (secondary endpoint). An unconstrained variance-covariance matrix will be used to accommodate within-participant effects. The method of Kenward and Roger [38] will be used to estimate the degrees of freedom for tests of all effects. Any baseline variables identified as substantially imbalanced between groups will be added to the models on an exploratory basis to confirm the robustness of the findings to this imbalance. Where distributional assumptions cannot be satisfied, bootstrapping methods or generalized mixed models (eg, binary MMRM) may be used to confirm the robustness of the findings. MMRM constitutes an intention-to-treat analysis, as it includes all available data under the missing-at-random assumption. Between-group effect sizes will be estimated using the estimated model means and variances.

Secondary and additional outcome analyses will involve contrasts comparing changes from baseline to follow-up analyses of secondary outcomes (mental health knowledge, stigma, helping behaviors, and psychological distress) from baseline to other occasions of measurement, using an MMRM approach, as described above. If the intervention is found to be effective, exploratory analyses will examine evidence for moderation effects, that is, whether the intervention was more effective for certain subgroups of the sample. This may include teacher attributes such as gender or age and school characteristics such as ICSEA status.

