### Sample Size

The target sample size for this trial is 234 participants from at least 47 schools. This calculation is conservatively based on the participation of an average of 5 educators per school and an intraclass correlation of 0.07, which yields a design effect of 1.28. To detect a standardized effect size of 0.50, (a minimum of a moderate effect size is required to warrant future value and benefit of the program) with 80% power and α=.05 (2-tailed), an individually randomized trial would require 64 participants per arm. This number is inflated by the design effect to 82 to allow for clustering, with the recruitment increased to conservatively allow for attrition of up to 30%. This yields a minimum of 117 participants per arm.

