### Randomization and Blinding

Cluster randomization at the school level is used to avoid potential contamination and bias effects from other participants, reduce administrative tasks for schools, and enable implementation of the peer-to-peer component of the program. As such, all participants from the same school will be allocated to the same condition and complete the trial at the same time using randomly permuted block randomization with block sizes of 2 and 4. Schools will be assigned to either the intervention or control arm using a 1:1 allocation, stratified by school size (<400 or >400 students) and index of community socioeducational advantage (ICSEA) level (<1000 or >1000) as per a computer-generated randomization schedule. Randomization is conducted by a statistician not involved in the day-to-day running of the trial to avoid influence or bias. The research team will be aware of the allocation once registration is scheduled to begin because they are responsible for providing the link to participants for the intervention or control program study website. Participants will be unaware of which group they are allocated to during registration and baseline. Upon completion of baseline, they will be informed, via email, of their allocation. This is because the intervention participants will receive immediate instructions and access to the program, and the waitlist control participants will be asked to wait for their next survey.

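### On its ordinary reading, the one random school effect drops out of the baseline-to-posttest contrast, so the primary test is not protected if schools change differently over time

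*Protocol article*

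**What the plan says.** All references are to the Protocol article.

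- **Randomization and Blinding:** "Schools will be assigned to either the intervention or control arm using a 1:1 allocation". The school is the unit of randomisation.
- **Statistical Methods, model:** the fixed effects are time, condition and their interaction. Correlation is handled by "accounting for repeated assessments within individuals and a random effect to account for clustering within schools". At participant level, "An unconstrained variance-covariance matrix will be used to accommodate within-participant effects".
- **Statistical Methods, test:** the analysis is specified "with the critical test of effectiveness being planned contrasts of this interaction from baseline to postintervention", with follow-up as the secondary endpoint. Secondary outcomes use the same approach.
- **Statistical Methods, degrees of freedom:** "The method of Kenward and Roger [38] will be used to estimate the degrees of freedom for tests of all effects".
- **Sample Size:** the calculation assumes "an average of 5 educators per school and an intraclass correlation of 0.07, which yields a design effect of 1.28".

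The section names no school-by-time effect, school-level slope or cluster-robust variance. Nor does it use the word intercept.

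**The concern.** In a cluster-randomised trial, the standard error of the treatment comparison must include the variation between schools in the quantity compared. Here that quantity is change from baseline. A time-constant school effect describes how schools differ in level and says nothing about how they differ in change. Any school-level variation in change is absorbed into the participant residuals and treated as independent between colleagues. Kenward-Roger does not repair this, because it works within the covariance model it is given and cannot restore a missing component.

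The article gives reasons why colleagues might change together. A school's participants all start in the same wave, and waves start on different dates. COVID-19 closures were affecting schools. Participants may report well-being programs implemented during the trial. The intervention includes optional coaching between colleagues. If change is correlated within schools, the primary p-value is too small and the interval too narrow, and the secondary contrasts share the fault.

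**Working it through.** **1. The plan's own figures.** For an effect of 0.50 SD, 80% power and two-sided α of 0.05, the t-based calculation gives 64 per arm. The design effect is 1 + (5 − 1) × 0.07 = 1.28. Then 64 × 1.28 = 81.9, rounded to 82; 82 / 0.70 = 117.1, stated as 117 per arm or 234 in total; 234 / 5 = 46.8, so 47 schools. These reproduce.

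**2. Cancellation.** For school s, person i and time t, write y = μ(arm, t) + u_s + e_it, where u_s has variance σ_s² and e has participant covariance Σ. The change is y_1 − y_0 = [μ(arm, 1) − μ(arm, 0)] + (e_1 − e_0), and u_s is gone. In matrix form, with c = (−1, 1), c′(σ_s² 11′)c = 0. With complete data and equal school sizes, the model variance of the contrast is c′Σc (1/n_1 + 1/n_0), with no school term. Unequal school sizes and missing visits bring the school term back only slightly.

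**3. Consequence if change is clustered.** If the ICC of change is ρ_Δ and m educators per school contribute, the true variance is larger by D = 1 + (m − 1)ρ_Δ. A nominal 5% test then rejects with probability about 2[1 − Φ(1.96/√D)]. Example: m = 5 and ρ_Δ = 0.07 give D = 1.28, 1.96/√1.28 = 1.732, and 8.3%.

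The values of ρ_Δ are assumptions. The values of m are the planned 5, the enrolled 295/71 = 4.15, and 4.15 × 0.70 = 2.9 after 30% attrition.

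| ρ_Δ | m = 5 | m = 4.15 | m = 2.9 |
|---|---|---|---|
| 0 | 5.0% | 5.0% | 5.0% |
| 0.02 | 5.9% | 5.7% | 5.4% |
| 0.035 | 6.6% | 6.3% | 5.8% |
| 0.07 | 8.3% | 7.6% | 6.6% |
| 0.10 | 9.8% | 8.8% | 7.3% |

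**4. Null simulation.** Assumptions: ICC 0.07 at each time point, within-person correlation 0.6, two time points, REML fits, 1,000 runs per cell. The t reference used completers − 2 degrees of freedom for the intercept model and schools − 2 for the school-by-time model, as an approximation to Kenward-Roger. Monte Carlo error is about 0.7 to 1 point. The implied ρ_Δ is 0.07(1 − r) / [0.07(1 − r) + 0.93 × 0.4], where r is the correlation of a school's effect between baseline and posttest.

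| r | ρ_Δ | Intercept only, 47 × 5, complete | School-by-time, same | Intercept only, 71 schools, 30% attrition | School-by-time, same |
|---|---|---|---|---|---|
| 1.0 | 0 | 4.1% | 3.1% | 4.0% | 3.1% |
| 0.8 | 0.036 | 6.9% | 4.4% | 6.9% | 4.1% |
| 0.5 | 0.086 | 8.7% | 3.9% | 10.5% | 5.4% |
| 0 | 0.158 | 12.6% | 4.6% | 13.1% | 6.0% |

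At r = 0.5 the intercept model's mean standard error was 0.117 against an empirical SD of 0.134 (47 schools), and 0.122 against 0.144 (71 schools).

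A separate simulation with three time points, 71 schools, complete data and 1,800 to 2,000 runs per scenario gave 5.2%, 7.3%, 8.3% and 12.2% for the intercept model at the same four values of r. With a school-by-time effect it gave 4.6%, 5.8%, 4.6% and 5.3%.

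**The case against.** **Inflation is not a fact of this design.** A reader might infer that the primary test has a false-positive rate above 5% as it stands. The article does not support that. With constant school effects the planned model is correct, and the simulated rate was 4.0% to 5.2%. Inflation requires schools to differ in their change over 10 weeks, and the article gives neither an ICC of change nor a correlation of school effects over time. This objection stands, and the conclusion is conditional because of it.

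**The largest figures are extreme.** Rates of 12% to 13% assume no correlation between a school's effect at baseline and 10 weeks later, with the same staff in the same school. They should not be quoted as the expected size. Applying the sample-size ICC of 0.07 to change scores is likewise an assumption.

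**The mechanisms are plausible, not shown.** Coaching is optional and reaches only the intervention arm during the trial. A stable school policy cancels; only changes in policy matter. Closures are mentioned only in general terms.

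**The form of the random effect may be fixed elsewhere.** The article does not say intercept, and an analysis plan that is not shown may specify more. That is possible, but an intercept is the usual meaning of one random effect for a cluster. The article spells out the covariance over time for participants only.

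**The design effect is not a strict contradiction.** A reader might take the 1.28 as proof that the two sections conflict. It may simply be conservative sizing. What remains is that the clustering allowed for in the sample size is not carried into the contrast tested.

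**Conclusion.** The point holds in conditional form. On the ordinary reading, the school term cancels from the primary contrast, exactly with complete data and equal school sizes and nearly so otherwise. The primary and secondary change contrasts are then valid only under an unstated assumption that school effects do not move between assessments. Under that assumption the error rate is nominal. Otherwise it exceeds 5%: about 5.4% to 10% for an assumed ICC of change of 0.02 to 0.10 and 2.9 to 5 educators per school. Since the school is the randomised unit and correlated change is plausible, the primary analysis should not depend on that assumption.

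**What to change.** In Statistical Methods, replace the single school term with a random school effect plus a random school-by-time effect, or with a school-level covariance matrix across the three time points. Keep the unconstrained participant covariance, and take the Kenward-Roger degrees of freedom for all contrasts from this model. Apply the same structure to the secondary outcomes.

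An alternative is to model posttest and follow-up with baseline as a covariate and school effects that may vary by time. This keeps the school effect in the tested comparison. It is not equivalent, because it replaces the prespecified interaction contrast with a different model and test.

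**Cost.** One more variance component, which may be estimated at zero, and a slightly wider interval. Where the extra term was not needed (r = 1), the mean standard error rose from 0.112 to 0.117 with 47 schools and from 0.117 to 0.122 with 71 schools, about 4%, and the test was somewhat conservative at 3.1%. No new data are needed. Enrolment of 295 educators in 71 schools, against a target of 234 in 47, leaves room for this. The article describes follow-up as still to be completed, so the change can be fixed before the outcome analysis.

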### Hypotheses

The primary hypothesis is that educators who are allocated to receive the BEAM program will report significantly higher levels of confidence at posttest (primary endpoint) when compared with the waitlist control condition and that these effects will be sustained at follow-up. It is also hypothesized that educators who receive the BEAM program will report greater improvements in mental health knowledge, stigma, and psychological distress at posttest and a greater frequency of helping behaviors at follow-up, when compared with those in the control condition.

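### The primary contrast is a valid difference in mean change, but it is less precise than a comparison that adjusts for or constrains baseline; the loss depends on a baseline-posttest correlation the article does not give

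*Protocol article*

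**What the plan says.** **Analysis (Statistical Methods).** The primary model is a mixed model for repeated measures with an unconstrained within-person covariance and a random effect for school. The fixed effects are time, condition and their interaction, "with the critical test of effectiveness being planned contrasts of this interaction from baseline to postintervention"; the contrast to follow-up is secondary. Baseline is therefore one of the modelled responses, and each arm has its own baseline mean. Baseline variables enter as covariates only if they turn out imbalanced, and then only as an exploratory check. The secondary outcomes follow the same approach.

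**Hypothesis (Hypotheses).** Educators given the program "will report significantly higher levels of confidence at posttest (primary endpoint" than the waitlist arm.

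**Sample size (Sample Size).** The aim is given as "To detect a standardized effect size of 0.50", and the starting figure is that, "with 80% power and α=.05 (2-tailed), an individually randomized trial would require 64 participants per arm". The clustering inputs are "an average of 5 educators per school and an intraclass correlation of 0.07, which yields a design effect of 1.28". Multiplying by the design effect gives 82 per arm, and a 30% allowance for dropout leads to the final figure: "This yields a minimum of 117 participants per arm". No correlation between baseline and posttest confidence appears here or anywhere else in the article.

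**Enrolment (Results).** 295 educators from 71 schools completed baseline, against a target of 234 from 47. The fourth wave was cancelled.

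**The concern.** When each arm has its own mean at every occasion and the covariance is unconstrained, the baseline-to-posttest interaction is, for complete data, the difference between arms in mean change. That estimate subtracts the whole observed baseline difference between arms. Under randomization that difference is chance alone, and the best correction subtracts only the fraction r of it. Subtracting all of it adds noise.

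The interval for the primary effect is therefore wider than the same data allow, and likewise for the secondary outcomes. The power statement is also for a test with outcome variance 1, whereas the planned contrast has variance 2(1-r). Whether the contrast reaches the stated 80% thus depends on a quantity the calculation did not use.

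**Working it through.** **Inputs.** From Sample Size: effect 0.50 SD, two-tailed alpha 0.05, power 80%, 5 educators per school, intraclass correlation 0.07, 82 analysed and 117 recruited per arm, 30% attrition. From Results: 295 enrolled, 71 schools. The correlation r is not in the article; 0.3 to 0.7 is an assumed range.

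**Step 1: the plan's own figure.** A two-sample t calculation at d = 0.50 gives 64 per arm (power 80.1%; 63 gives 79.5%). Design effect: 1 + (5 - 1) × 0.07 = 1.28. 64 × 1.28 = 81.9, so 82. 82/0.70 = 117.1, stated as 117. 234/5 = 46.8, so 47 schools. The figures reproduce, and they describe a posttest-only comparison.

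**Step 2: precision.** On a scale where the posttest SD is 1 and the variance is equal at both occasions:
- change contrast: v = 2(1 - r)
- baseline-adjusted or baseline-constrained: v = 1 - r²
- ratio, adjusted to change: (1 + r)/2, so the information lost with complete data is (1 - r)/2.

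If the mixed model also uses the baselines of people lost later, with retained fraction f = 0.7, the change contrast has v = (1 - r²) + f(1 - r)². The loss becomes f(1 - r)/[(1 + r) + f(1 - r)]. At r = 0.5 this is 0.35/1.85 = 19%.

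**Step 3: power.** Normal approximation: power = Φ(0.5 × √(n_eff/(2v)) - 1.96).
- Planned: n_eff = 82/1.28 = 64.06 per arm.
- Enrolled: 295/2 = 147.5 per arm; × 0.7 = 103.25. Mean cluster 295/71 = 4.15, design effect 1 + 3.15 × 0.07 = 1.22, n_eff = 103.25/1.22 ≈ 84.6.

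| r | Loss, complete data | Loss, all baselines, 30% attrition | Planned: change | Planned: adjusted | Enrolled: change | Enrolled: adjusted |
|---|---|---|---|---|---|---|
| 0.3 | 35% | 27% | 66.7% | 84.3% | 78.5% | 92.6% |
| 0.4 | 30% | 23% | 73.3% | 87.0% | 84.3% | 94.4% |
| 0.5 | 25% | 19% | 80.8% | 90.4% | 90.2% | 96.4% |
| 0.6 | 20% | 15% | 88.6% | 94.3% | 95.3% | 98.2% |
| 0.7 | 15% | 11% | 95.5% | 97.7% | 98.7% | 99.5% |

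The power columns use complete-data variances with the full design effect applied to the change.

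**Step 4: the r below which the change contrast has less than 80% power.**

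| Assumption | Planned sample | 295 enrolled, 30% attrition |
|---|---|---|
| Full design effect on the change | 0.49 | 0.33 (0.36 with 1.28) |
| All baselines used | 0.44 | 0.24 |
| School effect constant over time, cancels from the change | 0.35 | 0.18 |

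The article names a single school random effect, which points towards the last row. In the other direction, if school effects at baseline and posttest were unrelated, planned-sample power for the change would be 72.7% at r = 0.5 and 78.4% at r = 0.6. A single time-constant school effect does not describe that case.

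**The case against.** The strongest defence is that nothing here is an error. Averaged over randomizations, the expected baseline difference is zero, so the difference in change and the difference at posttest estimate the same effect, and the contrast is unbiased with the right type I error. The section on the primary outcome also says that scores are compared both over time and between arms, which the interaction does. The sample size is internally correct and is conservative for the planned test once r is about 0.5 or more. Enrolment has exceeded the target. All of this stands.

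Three stronger readings are tempting, and the article does not support them.

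- **The trial is underpowered.** This needs a value of r that the article does not give. On the enrolled numbers with 30% attrition it needs r below about 0.33, and lower still if all baselines are used or the school effect cancels.
- **The analysis tests something other than the hypothesis.** The target is the same under randomization; only the precision differs.
- **A chance baseline imbalance biases the result.** In a given realized trial the change contrast does over-correct for a chance difference. That is a conditional effect and one face of the lost precision, not bias over randomizations.

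A fair practical objection is that moving baseline from response to covariate drops participants who have baseline data only, while the article rests its intention-to-treat claim on using all available data. The constrained form avoids this. What the defence does not remove is that the loss exists at every r below 1, and that a larger sample makes a shortfall less likely without recovering it.

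**Conclusion.** The point holds as an avoidable loss of efficiency in a valid primary test. Its size is (1 - r)/2 of the information with complete data (30%, 25% and 15% at r = 0.4, 0.5 and 0.7), or about 23%, 19% and 11% when all baselines are used with 30% attrition. The stated 80% power is at risk only for low r: below about 0.5 at the planned 82 analysed per arm with the design effect of 1.28 on the change, and below about 0.33 at best-documented enrolment with 30% attrition.

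The figures assume equal variances at the two occasions, the article's effect size and intraclass correlation, equal arms and an r chosen for illustration. The gain also assumes that baseline means differ between arms only by chance. Schools are randomized before educators register, but the section on randomization and blinding says participants do not know their allocation until baseline is complete, which supports that assumption.

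**What to change.** Keep the mixed model with all three occasions, the unconstrained covariance, the school effect and the Kenward-Roger degrees of freedom, but constrain the baseline means to be equal across arms: include time, condition-by-posttest and condition-by-follow-up, with no condition term at baseline. The alternative is to model posttest and follow-up as responses, with baseline confidence by time as a covariate. The constrained form is preferable because it keeps participants with baseline data only and so preserves the claim to use all available data.

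Name the adjusted difference at posttest as the primary test and the one at follow-up as the secondary test. Use the same form for the secondary outcomes. Keep the change contrast as a supportive analysis.

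The cost is a change of analysis wording. Baseline confidence is already collected, and educators who do not complete the baseline survey are withdrawn, so no new data are needed. Because baseline was complete and treatment under way when the article was written, record the change as a dated amendment before outcomes are compared between arms. The sample size need not be redone.
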